## Methods / design

The study follows a longitudinal triple cross-sectional design (pre-post-post). It is based on three consecutive data collection phases, conducted in three clinics of a large academic teaching hospital in Germany. Data will be collected in each of the three clinics 2 months before the implementation (t0), as well as 6 months (t1) and 12 months (t2) after the implementation of the PP. Each of the three clinics has an eight-week period allocated for data collection to achieve the targeted case numbers described below. Quantitative data from surveys of patients (A) and physicians (B), qualitative data from interviews with patients and physicians (C), as well as medical history documentation (D) and administrative data from a participating clinic (E) are used to answer the research questions (Fig. 2). Each of the research questions (A) – (E) will be presented in detail in the following, including detailed case number calculations or sampling strategies.

**Fig. 2 Fig2:**
[figure not shown]
MAiBest study design

A)Analysis of determinants of patients PP usage

The trend survey at the three measurement time points (t0; t1; t2) allows for the depiction of determinants of PP usage and the expected changes in these determinants over time. The t0 survey captures the clinic-specific heterogeneity of patient-related determinants for PP use and enabling an adjustment of the trend analysis for these baseline values from t0. This facilitates the examination of trends within each clinic and allows for comparisons between the three clinics. Patients treated in the three clinics at the three measurement time points (t0; t1; t2), whether inpatient or outpatient, will receive a paper-based questionnaire with additional, optional access to a digital version. These questionnaires include items measuring patient-related determinants and, additionally, usage behavior in t1 and t2. The patient surveys are based on existing and validated scales (e.g. digital literacy [26], technology acceptance [20], or if not possible, on items developed according to methodological standards [23]. Additionally, socioeconomic and sociodemographic factors (e.g., age, gender, education, income) are recorded for later adjustment.

The sample size calculation results in a required rounded *N* = 200 patients per measurement time point per clinic (pooled total *N* = 1800). This is based on an assumed weak effect size for Cohen's D of 0.2 with 80% power and a significance level of 0.05 for a (1) two-sided independent two-sample t-test for the comparison between clinics at each measurement time point (total *N* = 393 at each time point for the comparison between two clinics, rounded *n* = 200 per clinic) and (2) for the comparison within the clinic across measurement time points in a two-sided paired t-test (required *n* = 198 per time point). The data analysis is performed using descriptive and inferential statistics, adjusting for previously collected socioeconomic and sociodemographic characteristics, conducted with the statistical software SPSS^©^.

B)Analysis of determinants of physicians PP usage

All physicians working in the three clinics at the three measurement time points (t0; t1; t2) receive digital questionnaires. These questionnaires include questions to measure physician-related determinants and additionally, in t1 and t2, questions regarding usage behavior. The surveys of physicians are based on already existing and validated scales (e.g. digital literacy [26], technology acceptance [20], or, if not possible, on items developed according to methodological standards [23]. Additionally, socioeconomic and sociodemographic factors (e.g., age, gender, work experience) are recorded for later adjustment. Due to the legal situation, physicians must inevitably use the PP in their everyday work. Nevertheless, they can use the PP, in this case the DAC, differently depending on which type of innovation adopter they belong to according to the DOI. For example, the *late majority* may only use the absolute basics, mandatory functionalities of the PP while the *innovators* also use additional advanced features, which may be optional to use. Therefore, in this project, the perceived benefit of the DAC is examined as the dependent variable, instead of the binary actual use, as it is done for the patients. Due to the organizational pressure to use, a stronger effect on physician PP usage can be expected. Based on an assumed effect size of Cohen’s D = 0.35, a power of 80%, and a significance level of 0.05 in a two-sided paired t-test, the required sample size is *N* = 66 physicians per time point, cumulated across the three clinics. A comparison of physicians between clinics at each time point will not be conducted due to the otherwise higher required sample size. The invitation to participate and access to the digital questionnaire will be distributed through internal channels, emphasizing the practical relevance of the survey for the medical staff and positively influencing the willingness to participate. The data analysis will be conducted using descriptive and inferential statistics, adjusting for socioeconomic and sociodemographic characteristics, and performed with the statistical software SPSS^©^.

C)Analysis of barriers to PP usage and reasons for non-usage

Interviews will be conducted with patients who are treated on an outpatient or inpatient basis at the three clinics during the measurement time points t1 and t2 and used or did not use the digital anamnesis. In addition, interviews will be conducted with physicians who are working on an outpatient or inpatient basis at the three clinics during the measurement points t1 and t2 and used or did not use the digital anamnesis. Based on Rogers' DOI [25], the reasons for non-usage and experienced barriers during the use of the DAC can change with the PPs increasing existence. Therefore, interviews will be conducted at both t1 and t2. The semi-structured interviews will include questions regarding the subjectively perceived barriers during the usage or reasons for non-usage.

In each of the three clinics, a total *n* = 12 interviews with patients will be conducted at each measurement time point (t1 & t2). Purposeful sampling will be employed, varying different patient characteristics (e.g., age, education) to achieve theoretical saturation [22]. The total of *N* = 72 interviews will be conducted either in person, for example, during treatment at the clinic's premises, or by telephone according to the participants' preference. Moreover, *n* = 4 interviews with physicians will be conducted in each of the three clinics at each measurement time point (t1 & t2). Purposeful sampling will be employed, varying different physician characteristics (e.g., age, specialty, ambulatory/inpatient setting) to achieve theoretical saturation [22]. The total of *N* = 24 interviews will take place in the clinics and, if possible, during working hours. This reduces the effort for the interviewees and increases the willingness to participate. Depending on the participants' preference, the interviews can also be conducted by phone. All interviews, estimated to last 45 min, will be recorded, transcribed, and anonymized. Subsequently, the data will be analyzed using content analysis [19] with the assistance of the MAXQDA^©^ 2024 software. 

D)Analysis of actual PP usage

The anamnesis documents in each of the three clinics will be analyzed at the three measurement time points (t0; t1; t2). In t0, only the physician-filled medical history will be considered, while in t1 and t2, the now via the PPs DAC tool patient-filled medical history will be examined. In each clinic and at each time point, an intentional sampling approach [22] will analyze approximately *n* = 30 documents of patients treated in the respective clinics during the survey periods. This approach results in a total of *N* = 270 documents to be analyzed. These will be examined using document analysis according to Prior [24], allowing statements about changes in the quality and content of the anamnesis documentation [4]. Haas [13] describes three functional levels of clinical documentation. In its primary function, documentation supports the preparation and monitoring of the actual treatment process. In its secondary function, documentation can also serve as a basis for billing purposes or legal obligations. In its tertiary function, documentation is used to answer scientific questions in the field of biomedicine or health services research [13]. Depending on which of the three functional levels is considered, different criteria are suitable for making statements about the quality of the documentation. For documentation in patient records, the U.S. Institute of Medicine identified completeness, readability, accuracy, and informativeness as the most important criteria for high-quality documentation [9]. Weiskopf & Weng [30] also highlighted completeness as the most important criterion for the quality of documentation in electronic patient records, especially regarding the described secondary and tertiary functions of documentation. Wurster et al. [32] further confirmed completeness as the most commonly used criterion for operationalizing documentation quality when investigating the transition from paper-based to electronic documentation and as actually receptive to change through the implementation of digital innovations [31]. In a first step, the contents of the documentation are recorded. This involves examining whether there is a change regarding the intended information to be documented (e.g., food intolerances, vaccination status) and how this information can be documented (e.g., checkboxes, free text). Based on this, an exploratory approach will be used to determine whether and how the quality of those documents can be reflected through the completeness of relevant information (as dimension of data quality). Completeness is operationalized as a percentage indicating, for each time period and clinic, whether specific information is filled in (documented vs. not documented) across all records [32]. The analysis in the pre-post-post comparison allows statements about how physician-filled and patient-filled medical histories differ and whether the expected changes over time, according to Rogers [25], are evident.

E)Analysis of changes in internal administrative and clinical parameters

In light of the fact that it is unclear to what extent the DOI can be applied to PP, it is unclear to what extent the hospital data collected for administrative purposes is suitable for making statements regarding potential improvements in care. To identify outcomes relevant for future research projects, an exploratory analytical approach is applied to the hospital data collected for administrative purposes from one participating clinic. If the utilization of PP leads to improvements in clinical outcomes, these improvements would be reflected in the administrative and clinical management data. For instance, parameters mentioned by Dumitrascu [10] such as the 30-day readmission rate, inpatient mortality, or 30-day mortality are analyzed. The data consist of administrative data for all outpatient and inpatient patients within a month at the three measurement points (t0; t1; t2). Data analysis involves descriptive and inferential statistics to compare the means of the examined parameters regarding potential differences at the three measurement points. The results provide initial indications of whether the parameters investigated here are suitable for assessing potential impacts of the PP on clinical outcomes in further research projects.

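### The 393 patients given as the total for a two-clinic comparison is the number needed in each clinic, so 200 per clinic gives about 51% power at d = 0.2, not 80%

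*Protocol article*

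**What the plan says.** The sample size paragraph of the protocol article (Methods / design, part A, determinants of patients' portal use) sets a target of "200 patients per measurement time point per clinic (pooled total" N = 1800). It rests on an "assumed weak effect size for Cohen's D of 0.2 with 80% power and a significance level of 0.05", applied to two tests.

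- The first is a "two-sided independent two-sample t-test for the comparison between clinics at each measurement time point". Its requirement is given as a total N of "393 at each time point for the comparison between two clinics, rounded" to n = 200 per clinic.
- The second is "for the comparison within the clinic across measurement time points in a two-sided paired t-test (required" n = 198 per time point).

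The same part says that the design permits comparisons between the three clinics. The Theory section lists the link between determinants and clinical context as an open question.

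**The concern.** An independent two-sample t-test at d = 0.2 with 80% power is known to need nearly 400 per group. A total of 393 for two groups is about half of that, and the step from 393 to 200 per clinic shows that the figure was divided by two. If 393 is really the per-group requirement, the stated 80% power does not apply to the clinic comparison at the planned effect size.

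A true difference of d = 0.2 between two clinics would then be missed about half the time at any one time point. A reader who trusted the 80% could take a non-significant clinic difference as a sign that determinants do not depend on the clinic. That matters here because the article's Discussion hopes to generalise time-constant determinants to other hospitals.

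**Working it through.** **Inputs**, all from the sample size paragraph in part A: d = 0.2; two-sided alpha 0.05; power 80%; independent two-sample t-test; two clinics of equal size; planned n = 200 per clinic per time point. No dropout allowance is stated; 200 is described only as rounded.

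**1. Reproducing 393.** In the normal approximation, n per group = 2 × (z for 0.975 + z for 0.80)² / d² = 2 × (1.960 + 0.842)² / 0.04 = 392.4, rounded up to 393. The exact (noncentral t) solution is 393.4 per group, rounded up to 394. The printed 393 is therefore the per-group answer.

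**2. Total for two clinics.** 2 × 393 = 786 (normal) or 2 × 394 = 788 (exact). Neither is 393. Halving the printed figure gives 393 / 2 = 196.5, which the article rounds to 200.

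**3. Power at the planned size.** With 200 per clinic, the expected test statistic is d × √(n/2) = 0.2 × √100 = 2.0. Normal approximation: Φ(2.0 − 1.960) = Φ(0.040) = 51.6%. Exact: 51.4%.

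**4. Effect detectable with 80% power at 200 per clinic.** d = (1.960 + 0.842) / √100 = 0.280; exact value 0.281.

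**5. Could another reading rescue a total of 393?**

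| Variant | Result |
|---|---|
| One-sided test | 310 per group, 620 in total; power at 200 per clinic 63.7% |
| One clinic against the other two pooled (200 vs 400) | power 63.5% |

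Neither variant gives a total of 393 or 80% power at 200 per clinic, and the article specifies a two-sided test of two clinics.

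**6. The second basis.** The paired t-test at d = 0.2 (on the paired difference) needs 198.2. The printed 198 agrees, so the arithmetic error is confined to the between-clinic calculation.

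**The case against.** Four points can be made for the plan.

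- **No listed hypothesis is tested this way.** A1 to A3 concern change over the observation period, A4 compares planned inpatients with acute outpatients, and A5 concerns treatment frequency. This stands and limits the weight of the point. A reader might infer that A1 to A5 are underpowered. The article does not support that from this error: it states none of them as a clinic contrast at one time point, and it does not say whether A4 coincides with one.
- **The target of 200 has a second basis.** The paired figure of 198 reproduces. A reader might infer that N = 1800 falls, or must rise to 9 × 394 = 3546. That does not follow, because the target does not rest on the misread figure alone. The paired calculation does not give power between clinics, however, and whether a paired test suits a design described as cross-sectional is a separate question.
- **Covariate adjustment could recover power.** The analysis adjusts for socioeconomic and sociodemographic factors. To restore 80% at 200 per clinic, the covariates would have to explain about 1 − (0.2 / 0.281)² = 49% of the outcome variance. The article claims nothing of the kind.
- **80% power is not out of reach for every clinic comparison.** That is true: the shortfall is at d = 0.2, and for differences of about 0.28 or more the planned size gives 80% or better.

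None of these makes the printed total correct. Nor is it a detail left to a fuller document, since the article prints the figure with all its inputs. In part B, the article drops the clinic comparison among physicians because it would need a larger sample. By that standard, the patient comparison looks adequately powered only because of the halved figure.

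**Conclusion.** The statement is wrong as written. On the article's own inputs, the between-clinic test needs 394 patients per clinic (788 for two) at each time point. The planned 200 is about half of that. Power is about 51% at d = 0.2, and the effect detectable with 80% power is about d = 0.28. These figures assume a continuous outcome with equal variances, equal clinic sizes, full recruitment of 200 per clinic, no multiplicity adjustment for the three pairs of clinics, and no gain from covariates.

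The reach is limited to the stated sample size justification and the planned clinic comparisons at single time points. The error does not by itself invalidate the study total.

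A reader might also conclude that the clinic comparison must be replaced by one pooled over the survey waves. The article does not support that as a requirement. It asks for the comparison at each time point, in a study premised on change over time, and a pooled contrast answers a different question.

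**What to change.** **Required.** In part A, state that the between-clinic test at d = 0.2 needs 394 patients per clinic (788 for two clinics) at each time point. Keep N = 1800, and say that 200 per clinic gives about 51% power at d = 0.2, or 80% power for d of about 0.28. Add that a non-significant clinic difference at a single time point will not be read as evidence of no difference; reporting confidence intervals would make this visible.

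**Optional.** A clinic contrast pooled over waves can be added as a supplementary analysis. Over t1 and t2 (400 vs 400) power at d = 0.2 is about 81%. Over all three waves (600 vs 600, determinants only, since use is not measured at t0) it is about 93%. The assumptions must be stated:

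- The difference averages 0.2 over the pooled waves. If it averages 0.15, 400 vs 400 gives about 56%.
- Each wave contains different patients.
- The outcome is continuous, whereas part B describes patient use as binary.
- There is no multiplicity adjustment. With alpha of 0.05/3 for three pairs of clinics, shown only as an illustration, the figures fall to about 67% and 86%.

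**Cost.** A few sentences of corrected text and no extra patients. The drawback is a less favourable power statement for the per-time-point clinic comparisons.

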**Methods:**

The project investigates the use of the patient portal in three different clinics of a large academic teaching hospital in Germany using a longitudinal study design with three cross-sectional time points (pre, post, post). Doctors and patients are surveyed about factors that predict the use of the patient portal and whether the strength of these factors changes over time. They are also interviewed about possible barriers they experience when using the patient portal or about the reasons why the patient portal is not used. Regression models and content analyses are used to answer the research questions.

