**Fig. 1 Fig1:**
[figure not shown]
Temporal diffusion of innovations [25]

Assuming, for example, that the individual’s digital literacy is a possible determinant of PP usage, it is expected that individuals with a markedly high level of digital literacy will adopt the PP particularly early (thus corresponding to the *innovators* type). However, the relevance of high digital literacy as a determinant of PP usage decreases over time. Accordingly, at a later stage, individuals with lower digital literacy would also adopt the PP (e.g. representing the *late majority* type). Regarding the research topic of PP, it is unclear whether the DOI can be applied. Even though one study has already shown that, following the DOI, the proportion of users of the PP increased slowly but steadily over time, implying an expected transition from only *innovators* among the users to additional *early adopters* among the users at a later date [33]. However, it is still unexplored, whether the relevance of potential determinants weakens over time or remain time constant. At the same time, it is uncertain whether and how the strength of the determinants or the extent of the expected weakening of these determinants is related to the clinical context (e.g., outpatient/inpatient) in which the PP is offered for use. In addition, there is no conclusive evidence as to whether and how the implementation of a PP and particularly the DAC affects documentation and treatment quality.

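### The patient sample size is justified by two comparisons of means that do not test the time hypotheses A1–A3 or the change-in-determinant question, so its 80% power does not carry over to them

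*Protocol article*

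**What the plan says.** The patient calculation in Methods / design, part A, gives a "required rounded *N* = 200 patients per measurement time point per clinic (pooled total *N* = 1800"). It rests on an "assumed weak effect size for Cohen's D of 0.2 with 80% power and a significance level of 0.05" for two tests. Test (1) is an independent two-sample t-test between clinics ("total *N* = 393 at each time point for the comparison between two clinics, rounded *n* = 200 per clinic"). Test (2) is "for the comparison within the clinic across measurement time points in a two-sided paired t-test (required *n* = 198 per time point").

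The questions are stated elsewhere:

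- **Abstract, Methods:** "Doctors and patients are surveyed about factors that predict the use of the patient portal and whether the strength of these factors changes over time", to be answered with regression models.
- **Background, Theory:** "it is still unexplored, whether the relevance of potential determinants weakens over time or remain time constant".
- **Table 1:** A1–A3 say that, among patients using DAC, the share with low digital literacy, low health literacy or low technology acceptance rises over the observation period. A4 and A5 are differences in use between patient groups, with no time element.
- **Part B, describing the patient outcome:** the physicians' outcome is perceived benefit "instead of the binary actual use, as it is done for the patients".

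On design, "The study follows a longitudinal triple cross-sectional design (pre-post-post"), and part A collects usage behaviour at t1 and t2 only.

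**The concern.** A sample-size statement vouches for a particular contrast. Here the contrasts are mean against mean: one clinic against another, or one time point against another in the same clinic. The time hypotheses need something else. Read literally, A1–A3 compare users at t1 with users at t2, so only the users among the 200 count. The question in the Abstract and Theory sections is a determinant-by-time interaction: does the gap in determinant score between users and non-users shrink from t1 to t2? That contrast has four cells. Patients surveyed at t0 carry no information on the association with use.

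The theory's time prediction is the project's central aim. The Discussion proposes that determinants found to be constant over time may hold across hospitals. If the test of change has low power, a determinant that does weaken will often show no significant change and could be reported as constant.

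**Working it through.** **Inputs from the protocol:** d = 0.2, two-sided alpha 0.05, power 80%; 200 per clinic per time point, hence 3 × 200 = 600 pooled; independent cross-sections; use known at t1 and t2 only.

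**Assumptions, because the protocol gives no figure:** the share u of patients using DAC (20%, 50% and 70% shown, equal at t1 and t2), and 0.2 SD as the size of the change, with SD = 1.

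**The plan's own figures**

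- Paired t-test: (1.960 + 0.842)² / 0.2² = 196.2 by the normal approximation and 198.15 by the t distribution. The stated 198 reproduces.
- Independent t-test: 2 × 196.2 = 392.4, or 393.4 by the t distribution. This is the number per group, whereas the protocol prints 393 as the total for two clinics. That is a separate error, as is the use of a paired test on cross-sections; correcting either would not settle this point.

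**Power formula:** Φ(0.2/SE − 1.96) + Φ(−0.2/SE − 1.96).

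**(a) Users at t1 against users at t2:** SE = √(2/(n·u)), with n patients per time point.

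| Use share | SE per clinic (n = 200) | Power | SE pooled (n = 600) | Power |
|---|---|---|---|---|
| 20% | 0.224 | 15% | 0.129 | 34% |
| 50% | 0.141 | 29% | 0.082 | 69% |
| 70% | 0.120 | 39% | 0.069 | 83% |

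Even if every patient used DAC, 200 against 200 gives SE 0.100 and about 52% power.

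**(b) Determinant-by-time interaction:** SE = √(2·[1/(n·u) + 1/(n·(1−u))]).

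| Use share | SE per clinic | Power | SE pooled | Power |
|---|---|---|---|---|
| 20% | 0.250 | 13% | 0.144 | 28% |
| 50% | 0.200 | 17% | 0.115 | 41% |
| 70% | 0.218 | 15% | 0.126 | 35% |

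A logistic interaction of 0.2 log-odds per SD at 50% use has SE = √(2/(n × 0.25)), which is 0.200 for n = 200 and 0.115 for n = 600, so the power is the same.

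**Sensitivity of (b) to the effect size, at 50% use**

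| Change | Per clinic | Pooled |
|---|---|---|
| 0.3 SD | 32% | 74% |
| 0.4 SD | 52% | 93% |
| 0.5 SD | 70% | 99% |

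**Change detectable with 80% power in (b)**, (1.960 + 0.842) × SE, at 50% and 20% use: 2.802 × 0.200 = 0.56 SD and 2.802 × 0.250 = 0.70 SD per clinic; 2.802 × 0.1155 = 0.32 SD and 2.802 × 0.1443 = 0.40 SD pooled.

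**Patients needed for 80% power in (b)** at 0.2 SD and 50% use: 8 × 196.2 ≈ 1,570 per time point, against 600 planned in all three clinics together.

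**The case against.** The strongest reply has four parts.

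1. *The protocol attaches its 80% to its two t-tests and never claims it for an interaction.* This is correct. A reader might infer that the protocol asserts 80% power for the interaction and is refuted; the text does not go that far. What stands is that part A offers no other basis for its sample size, so the time hypotheses are left without one.

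2. *The effect size has been moved to another quantity.* This is also correct. The protocol's 0.2 is a difference between two means, and it states neither a change in association nor a use share. A reader might conclude that power for the central test is simply 17% per clinic and at most 41% pooled. The documents do not support that: 41% is a maximum over the use share only, with the change fixed at 0.2 SD, and pooled interaction power is about 74% at 0.3 SD and 93% at 0.4 SD.

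3. *Table 1 is said to list every question addressed, and A1–A3 are worded as proportions among users, not as interactions.* This has force. On that reading pooled power is 34% to 83% over 20–70% use, and it passes 80% at the high end. A4 and A5 are not time-change tests and are untouched by this point.

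4. *Clinic-level trends are a stated purpose.* Part A promises trends within each clinic and comparisons between clinics, and the Theory section asks about clinical context. Reducing clinic results to description alone would cut against that, so it is not recommended.

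None of this rescues power within a clinic: at 0.2 SD no reading reaches 80% there. Nor is this a detail that can wait for an analysis plan, since the calculation and its 80% are printed in the article.

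**Conclusion.** Wrong as written: the basis of the sample size does not match the time hypotheses. The fault is one of target, not of arithmetic in the quoted figure, since 198 is right for the paired test named. Assuming a 0.2 SD effect, power within a clinic is 15% to 39% for users at t1 against users at t2, and 13% to 17% for the interaction, over 20–70% use. Pooled, the ranges are 34% to 83% and 28% to 41%. These figures depend on the assumed effect size, the assumed use share, independent samples at t1 and t2, and the reading of A1–A3; they make no allowance for covariate adjustment. The firm part is that the printed 80% does not describe either test and, at the protocol's own 0.2, is not reached within any clinic.

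**What to change.** - State in part A that the 80% figure belongs to the two comparisons of means and does not apply to A1–A3 or to the question whether determinants weaken.
- Make the main analysis of that question one model of DAC use pooled over the three clinics, with clinic terms, the continuous determinant score and a determinant-by-time term for t1 against t2. Keep clinic-specific estimates with confidence intervals and a note on their low power.
- Replace the power statement for this question with the conditional ranges above, and with the interaction detectable at 80% power: about 0.32–0.40 SD pooled and 0.56–0.70 SD per clinic at 20–50% use. Print the assumed use share and effect size beside them.
- State that a non-significant change is not evidence that a determinant is constant over time; judge constancy from the confidence interval for the change.

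The cost is rewording and a less favourable stated power. No additional patients are required.

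### The within-clinic comparison over time is sized as paired although the waves are described as unlinked cross-sections: about 51% power at d = 0.2 with 200 per wave, not 80%

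*Protocol article*

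**What the plan says.** The Methods / design section opens with the sentence "The study follows a longitudinal triple cross-sectional design (pre-post-post". Part A calls the patient component a trend survey: "The trend survey at the three measurement time points (t0; t1; t2) allows for the depiction of determinants of PP usage". Recruitment is by attendance in each window: "Patients treated in the three clinics at the three measurement time points (t0; t1; t2), whether inpatient or outpatient, will receive a paper-based questionnaire". The article describes no panel, no re-contact of earlier respondents and no identifier joining one wave to the next.

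The sizing paragraph of part A gives a "required rounded *N* = 200 patients per measurement time point per clinic (pooled total *N* = 1800". It rests on an "assumed weak effect size for Cohen's D of 0.2 with 80% power and a significance level of 0.05" and on two comparisons. The first is between clinics at one time point, by an independent two-sample t-test. The second is "for the comparison within the clinic across measurement time points in a two-sided paired t-test", with the result "required *n* = 198 per time point".

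On the analysis itself, part A promises descriptive and inferential statistics adjusted for socioeconomic and sociodemographic characteristics. The Methods paragraph of the abstract names regression models.

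**The concern.** A paired t-test needs two measurements on the same person. Its sample size counts pairs, and it is smaller than the unpaired figure because a positive within-person correlation removes variance. In a repeated cross-section with no linkage there are no identified pairs, so that gain is not available. The planned total fits this reading: 3 clinics × 3 waves × 200 = 1800 patients, whereas a panel of 200 per clinic would be 3 × 200 = 600 patients seen three times.

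Change over time is the study's main theme, and part A promises trends within each clinic. The Discussion intends to generalise determinants that prove constant over time. If the within-clinic comparison has about even odds of detecting the assumed effect, a non-significant trend could be misread as constancy by someone who believes the power is 80%.

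**Working it through.** **Inputs.** From part A: d = 0.2, two-sided α = 0.05, power 80%, 198 required and 200 planned per clinic and time point. From Methods / design and part A: three cross-sectional waves with no linkage described.

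**Step 1. Reproduce the plan's figure.** For a paired t-test with standardised mean change dz, the normal approximation is n = ((z₀.₉₇₅ + z₀.₈₀)/dz)² = ((1.960 + 0.842)/0.2)² = 196.2. The noncentral t gives 198.15, which is the stated 198. A one-sided test would give 155.9, which does not match. So 198 is a number of pairs with dz = 0.2.

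**Step 2. What that assumes about correlation.** With d in between-patient SD units and within-person correlation ρ, dz = d/√(2(1 − ρ)). The two scales agree only at ρ = 0.5. For 198 true pairs and d = 0.2:

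| ρ | dz | power |
|---|---|---|
| 0 | 0.141 | 50.8% |
| 0.25 | 0.163 | 62.8% |
| 0.5 | 0.200 | 80.0% |
| 0.7 | 0.258 | 95.1% |

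**Step 3. Independent waves.** The required n per wave is 2((z₀.₉₇₅ + z₀.₈₀)/d)² = 2 × 196.2 = 392.4. The noncentral t gives 393.4, so 394 per wave per clinic.

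For 200 per wave, the noncentrality is d√(n/2) = 0.2 × √100 = 2.0, just above the critical value of about 1.97. Power is therefore close to one half: 51.4% with 200 per wave and 51.0% with 198.

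The effect detectable with 80% power at 200 per wave is 2.80 × √(2/200) = 0.28.

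**Step 4. Pooling the clinics.** With 3 × 200 = 600 per wave, the noncentrality is 0.2 × √300 = 3.46. Power is 93%, and the detectable effect is 2.80 × √(2/600) = 0.16. This is for a mean score over all respondents.

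**Step 5. What pooling means for A1 to A3.** These hypotheses in Table 1 concern patients who use DAC, and usage is asked only at t1 and t2. The relevant number is users per wave, and the article gives no expected uptake. Assumed values, pooled over clinics at d = 0.2:

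| Assumed uptake | Users per wave | Power |
|---|---|---|
| 20% | 120 | 34% |
| 30% | 180 | 47% |
| 50% | 300 | 69% |

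A1 to A3 are worded as proportions, so these values on the d scale are only a guide.

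**The case against.** The strongest reply is that the paired t-test appears only as a basis for sizing. That is right. A reader might infer that the study will analyse its waves with a paired test, or will pair unrelated records and get an arbitrary result. The article supports neither: it announces adjusted regression, and nothing says that records will be matched. What remains is that the only power claim for change within a clinic rests on that test. Covariate adjustment might recover some power, but the article gives no figure for it.

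A second reply is that some patients may answer in more than one wave. This also stands as far as it goes. Hypothesis A5 expects frequently treated patients, and repeat respondents are not excluded, so it would be too strong to say that the three waves certainly contain different people. But no linkage is described, and the stated 198 needs essentially every respondent to be paired.

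A third reply is that the between-clinic calculation supports 200 on its own. It does not. The plan gives "total *N* = 393 at each time point for the comparison between two clinics, rounded *n* = 200 per clinic", but the 393 in Step 3 is the requirement per group. Halving it leaves that comparison with about 51% power as well.

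Finally, the full protocol may say more. The point does not depend on an omission: the article states a test and a number that conflict with the design it describes.

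**Conclusion.** The point holds as a defect of the sample-size justification. A count of pairs has been applied to waves for which no pairing is described. The within-clinic comparison has about 51% power at d = 0.2 instead of the stated 80%. To reach 80% it needs about 394 patients per wave per clinic, or an effect of d = 0.28.

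This rests on two assumptions: d = 0.2 is in between-patient SD units, the scale of the plan's own independent-samples test, and the waves are analysed as independent.

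Two stronger readings should be resisted. The 51% is the power of the sizing comparison as stated, not of any hypothesis in Table 1. And the pooled 93% is no reassurance for A1 to A3: it needs all 600 respondents per wave to contribute, whereas those hypotheses concern DAC users at t1 and t2, with power that depends on an uptake the article does not give.

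**What to change.** 1. In the sizing paragraph of part A, replace the paired t-test with an independent-samples basis. State that 200 per wave gives about 51% power within a clinic at d = 0.2, and 80% at d = 0.28.
2. Specify that the waves are treated as independent samples in the announced adjusted regression, with wave, clinic and wave-by-clinic terms. Report within-clinic contrasts with confidence intervals, so that a non-significant trend is not read as no change.
3. Optionally, add a clinic-adjusted wave contrast pooled over the three clinics. Limit its 93% power (detectable d = 0.16) to mean scores over all respondents, and give A1 to A3 a separate power statement with an explicit uptake assumption. Making the pooled contrast primary would demote the stated within-clinic aim, so that choice belongs to the sponsor.

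The cost is rewording of the sizing and analysis text, with no extra patients. Clinic-specific trends would be openly labelled as lower-powered. Keeping 80% at d = 0.2 within each clinic would instead need 3 × 3 × 394 = 3546 patients against the planned 1800.
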